## Abstract

**Background:**

Subcutaneous administration of Ig (SCIg) has gained popularity as an alternative route of administration but has never been rigorously examined in chronic inflammatory demyelinating polyneuropathy (CIDP).

**Methods/design:**

The primary objective of the PATH study (Polyneuropathy and Treatment with Hizentra) is to determine the efficacy of two different doses of SCIg IgPro20 (0.2 g/kg bw or 0.4 g/kg bw) in a 24-week maintenance treatment of CIDP in comparison to placebo. The primary efficacy endpoint will be the proportion of patients who show CIDP relapse (1-point deterioration on the adjusted Inflammatory Neuropathy Cause and Treatment (INCAT) disability score) or are withdrawn within 24 weeks after randomization for any reason. IVIg-dependent adult patients with definite or probable CIDP according to the European Federation of Neurological Societies/Peripheral Nerve Society who fulfil the inclusion and exclusion criteria will be eligible. Based on sample-size calculation and relapse assumptions in the three arms, a sample size of 58 is needed per arm (overall sample size will be 350, of which 174 will be randomized). All eligible patients will progress through three study periods: an IgG dependency period (≤12 weeks) to select those who are Ig dependent; an IVIg restabilization period (10 or 13 weeks), which will be performed using the 10 % IgPro10 product; and an SC treatment period (24 weeks, followed by a 1-week completion visit after last follow-up). Patients showing IVIg restabilization will be randomized to demonstrate the efficacy of SCIg IgPro20 maintenance treatment over placebo. After completing the study, subjects are eligible to enter a long-term, open-label, extension study of 1 year or return to their previous treatment. In case of CIDP relapse during the 24-week SC treatment period, IgPro10 rescue medication will be offered. Safety, tolerability, and patients’ preference of Ig administration route will be examined.

**Discussion:**

The PATH trial, which started in March 2012, is expected to finish at the end of 2016. The results will increase knowledge about the efficacy, safety, and tolerability of SCIg in maintenance management of CIDP patients.

**Trial Registration:**

ClinicalTrials.gov, NCT01545076. Registered on 1 March 2012.

## Background

Chronic inflammatory demyelinating polyneuropathy (CIDP) is an acquired neuropathy with an assumed autoimmune-mediated pathogenesis [1]. CIDP runs a progressive, relapsing–remitting, or monophasic course and can lead to significant activity limitations and participation restrictions with a decrement in quality of life expectations [2–4].

An estimated two thirds of patients with CIDP need long-term treatment [5]. In a comparison of safety profiles, IVIg is the preferred long-term maintenance treatment over corticosteroids or plasma exchange in CIDP patients. An alternative route of Ig administration, subcutaneous Ig (SCIg), has been used successfully in patients with immunodeficiency syndromes for more than 25 years [6]. SCIg infusions are well tolerated, efficacious, and preferred by many of these patients [7–10]. Furthermore, this route of administration increases patient compliance, autonomy, and quality of life and leads to cost-savings [11–14]. Similar preference has been suggested in patients with CIDP treated with SCIg.

The development of highly concentrated Ig preparations and special pumps to administer larger volumes subcutaneously has also raised interest in this route of administration for patients with inflammatory neuropathies. Several case series [14–22], a relatively large, prospective, observational study [23] and one small, randomized, controlled trial [24], have reported clinical efficacy and safety of weekly SCIg to treat CIDP. A 1-year, open-label, follow-up study has suggested SCIg may be used as a long-term maintenance treatment in CIDP [25]. However, the efficacy, safety, and tolerability of weekly SCIg in CIDP have not been studied in well-controlled and adequately powered randomized clinical trials. The findings of the PATH trial are expected to increase the knowledge about the use of SCIg in the maintenance management of CIDP patients.

## Methods/design

The PATH trial is a randomized, multicenter, double-blind, placebo-controlled, parallel-group phase III study with three arms, aiming to investigate two different doses of SCIg IgPro20 (Hizentra®, CSL Behring, Bern, Switzerland) for maintenance treatment of patients with CIDP. The study began in March 2012 and is expected to finish at the end of 2016. The trial protocol has been approved by the ethics committees of all participating centers (listed in the Appendix). Protocol amendments are covered in a separate section below. The conduct of the trial was overseen by a steering committee and an independent data monitoring committee; committee members are listed at the end of the manuscript. This study is registered with ClinicalTrials.gov number NCT01545076.

### Primary objective

The primary objective is to determine the efficacy of IgPro20 in the maintenance treatment of CIDP patients.

### Secondary and exploratory objectives

To determine the efficacy, safety, and tolerability of IgPro20, with additional clinical outcome measuresTo determine the safety and efficacy of IVIg IgPro10 restabilization and rescue therapyTo determine health-related quality of life (HRQL) following treatment with IgPro20To explore additional safety and efficacy endpoints, serum IgG levels, and the effect of IgPro20 on nerve conduction

### Patients

#### Inclusion criteria

Adults (age ≥ 18 years) with definite or probable CIDP according to the EFNS/PNS criteria may enter the trial if they responded to IVIg treatment as assessed by the treating physician within 8 weeks before enrollment [26]. Written informed consent is obtained by the local investigator before entry into the study.

#### Exclusion criteria

Any polyneuropathy of other causes, including multifocal motor neuropathy; monoclonal gammopathy of uncertain significance with antimyelin-associated glycoprotein IgM antibodies; hereditary demyelinating neuropathy; polyneuropathy, organomegaly, endocrinopathy, monoclonal protein and skin change syndromes; lumbosacral radiculoplexus neuropathy; polyneuropathy associated with diabetes mellitus; polyneuropathy associated with systemic illnesses; or drug- or toxin-induced polyneuropathyAny other disease that may cause neurological symptoms and signs or that may interfere with treatment or outcome assessmentsSevere conditions that may interfere with an evaluation of the study product or satisfactory conduct of the study such as current malignancy or history of allogeneic bone marrow/stem cell transplant, cardiac insufficiency (New York Heart Association Classes III/IV), cardiomyopathy, significant cardiac arrhythmia requiring treatment, unstable or advanced ischemic heart disease, congestive heart failure or severe hypertension, chronic kidney disease stage IV and V, known hyperprolinemia, known bleeding disorders, severe skin disease at the planned injection sites, alcohol, drug or medication abuseHistory of thrombotic episodes within the 2 years before enrollment, such as pulmonary embolism, deep vein thrombosis, myocardial infarction, thromboembolic stroke or known hypercoagulable stateKnown allergic or other severe reactions to blood products including intolerance to previous IVIg, history of hemolysis after IVIg infusion, aseptic meningitis, recurrent severe headache, hypersensitivity, or severe generalized skin reactionTreatment with the following:Within 3 months before enrollment: plasma exchangeWithin 6 months before enrollment: cyclophosphamide, interferon, tumor necrosis factor–alpha inhibitors, fingolimod, or any other immunosuppressive medicationsWithin 12 months before enrollment: rituximab or alemtuzumabWith a change in treatment within 3 months before enrollment: methotrexate, azathioprine, or mycophenolate; patients on corticosteroids not on a maintenance dose (usually below 20 mg/day prednisone equivalent) and where the dosage is likely to be tapered during the duration of the trial; or patients requiring more than 1.6 g/kg IgG every 4 weeksPatients with the following laboratory results:Serum IgA level less than 5 % of the lower limit of normalPositive result at screening on any of the following viral markers: human immunodeficiency virus-1 or 2, or hepatitis B or C virusAbnormal laboratory parameters: creatinine greater than 1.5 times the upper limit of normal (ULN), blood urea nitrogen greater than three times the ULN if the increase is related to potential kidney disease, or hemoglobin less than 10 g/dLFulfilling the following general criteria: inability to comply with study procedures and treatment regimen; mental condition rendering the patient unable to understand the nature, scope, and possible consequences of the study; pregnancy or nursing mother; intention to become pregnant during the course of the study; female patients of childbearing potential either not using or not willing to use a medically reliable method of contraception for the entire duration of the study or not sexually abstinent for the entire duration of the study or not surgically sterile; participation in another clinical study or use of another investigational medicinal product within 3 months before enrollment; employee at the study site; or spouse/partner or relative of any study staff

### Study procedures

After being screened, all eligible patients will progress through three study periods: an IgG dependency test period (up to 12 weeks), an IVIg restabilization period (10 or 13 weeks), and an SC treatment period (25 weeks; Fig. 1).

**Fig. 1 Fig1:**
[figure not shown]
Study design. Diagram explains how patients flow through the different study periods. *IgG* immunoglobulin G, *IVIg* intravenous immunoglobulin, *INCAT* Inflammatory Neuropathy, Cause and Treatment

#### IgG dependency test period

In this period, no IgG treatment is given. Patients are monitored by collecting grip strength, Inflammatory-Rasch-built Overall Disability Scale (I-RODS), and INCAT total score data every 2 weeks, alternating by a site visit or by phone. Any patient showing a clinically meaningful deterioration that is confirmed by the investigator at the site will enter the IVIg restabilization period immediately. A clinically meaningful deterioration is defined as a total INCAT disability score increase by ≥ 1 point, I-RODS deterioration by ≥ 4 points (using the centile metric), or a mean grip strength deterioration by ≥ 8 kiloPascal (kPa) in one hand using the handheld vigorimeter [27–30].

Patients will be instructed on how to self-assess grip strength and I-RODS at home as part of a weekly diary. Patients will be performing three assessments for each hand in arbitrary order (with approximately 30 seconds rest between each assessment) on a daily basis and at a fixed time during the day. The mean grip strength for each hand will be used to determine IgG dependency.

Patients who have stable disease or who show improvement will be asked at week 4 to delay the next IVIg administration and to continue with self-assessment of grip strength and I-RODS at home. Patients who do not show signs of IgG dependency after a maximum of 12 weeks will be withdrawn from the study.

#### IVIg restabilization period

In this period, patients will receive IVIg IgPro10 (Privigen®, CSL Behring, Bern, Switzerland) for up to 13 weeks at the study site. The total dose/volume of IgPro10 will be calculated based on the patient’s body weight (bw) with a maximum of 200 g. The loading dose is 2 g/kg (week 1) and 1 g/kg at week 4, 7, and 10 and, if necessary, week 13. The infusion rates are in conformity with the recommended rates for IgPro10 and with the market authorization for IgPro10 (Privigen®) with a maximum of 100 g per infusion day. [31]

Only patients whose INCAT total score improves to at least the INCAT total score recorded at the screening visit (i.e., ≥ INCAT score at screening) and who maintain a stable INCAT total score at weeks 7 and 10 (or at weeks 10 and 13) are eligible for randomization. All other patients will not be randomized and will be withdrawn from the study.

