### Outcome assessment

#### Primary outcome

Primary outcome is defined as the percentage of patients who have a CIDP relapse during SC treatment or who are withdrawn from the study during SC treatment for any reason.

CIDP relapse is defined as a deterioration (i.e., increase) by at least 1 point in the total adjusted INCAT score during the SC treatment period visit compared with baseline. Baseline scores are defined as the scores assessed at the end of the IVIg restabilization period. The INCAT disability scale ranges from 0 (healthy) to 10 (unable to make any purposeful movements with arms or legs) [32].

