#### Efficacy evaluation secondary outcomes

An overview of the planned analyses is provided in Table 2. Time to improvement during the IVIg restabilization period will be analyzed separately for INCAT total score (decrease by ≥ 1 point), mean grip strength (increase by ≥ 8 kPa), dominant/nondominant), and I-RODS (increase by ≥ 4 points), as well as overall using Kaplan-Meier estimates. For the overall analysis, if a subject has multiple dates of improvement, the first will be used. Subjects who do not record an improvement will be censored at the date of their last visit. Analyses will be based on the PSDS. Time to improvement after relapse in the SC treatment period will be analyzed on the INCAT total score using the RSDS. An overview of all other planned secondary analyses is provided in Table 2.

**Table 2 Tab2:** Analyses performed at each study period for secondary outcomes, IgG levels, and health-related quality of life variables

	Period (analysis set)		
	IVIg restabilization (PSDS)	SC treatment (ITTS, PPS)	IVIg rescue (RSDS)
INCAT			
Total	Overall: - Descriptive statistics - Change from reference visit - Time to first improvement on IgPro10: Kaplan-Meier estimates	- By treatment and by treatment and subgroup: - Descriptive statistics - Comparison between treatments of changes from reference visit: exact Jonckheere-Terpstra test^a^ - Comparisons between each IgPro20 dose group and placebo group, and the comparison between the two IgPro20 dose groups of changes from reference visit: Wilcoxon rank sum test^b^ - Time to CIDP relapse or withdrawal for any other reason: Kaplan-Meier estimates^c^	Overall: - Descriptive statistics - Change from reference visit - Time to improvement after CIDP relapse with IgPro10 rescue: Kaplan-Meier estimates
Mean grip strength (Dominant/non-dominant hand), MRC sum score, I-RODS			
	Overall: - Descriptive statistics - Change from reference visit - Time to first improvement on IgPro10: Kaplan-Meier estimates	By treatment and by treatment and subgroup: - Descriptive statistics - Comparison between treatments of changes from reference visit; exact Jonckheere-Terpstra test^a^ - Comparisons between each IgPro20 dose group and placebo group, and the comparison between the two IgPro20 dose groups of changes from reference visit; Wilcoxon rank sum test^b^	Overall: - Descriptive statistics - Change from reference visit

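### The INCAT criterion for randomisation contradicts itself: its words require recovery to the screening level, but the ≥ sign in the parenthesis points the other way on a scale where higher is worse

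*Protocol article*

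**What the plan says.** The section on the IVIg restabilization period sets two conditions for randomisation. The first is on level: the INCAT total score "improves to at least the INCAT total score recorded at the screening visit (i.e., ≥ INCAT score at screening"). The second is on stability: patients "who maintain a stable INCAT total score at weeks 7 and 10 (or at weeks 10 and 13) are eligible for randomization". For everyone else, "All other patients will not be randomized and will be withdrawn from the study".

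The direction of the scale is given under Primary outcome: "The INCAT disability scale ranges from 0 (healthy) to 10 (unable to make any purposeful movements with arms or legs"). The same section says "CIDP relapse is defined as a deterioration (i.e., increase) by at least 1 point in the total adjusted INCAT score", counted from the scores at the end of the restabilization period. The IgG dependency test counts a "total INCAT disability score increase by ≥ 1 point" as deterioration. The secondary analyses count improvement during restabilization as "INCAT total score (decrease by ≥ 1 point").

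**The concern.** The parenthesis is introduced as a restatement of the words before it, but on this scale it says the reverse. To improve to at least the screening level is to have no more disability than at screening, so the score must be no higher. The printed sign asks for a score no lower.

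The sign sits in the rule that separates patients who are randomised from those who are withdrawn. The score on leaving that period is also the reference for every relapse in the primary endpoint. If the sign had been used as the test, patients who had not regained their screening level could have entered the randomised phase, and patients who had done better than at screening would have been sent out. That would conflict with the purpose stated in the Discussion under Design, which is to show that IgPro20 maintains the INCAT improvement gained on IVIg.

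**Working it through.** The article gives no figure to reproduce here. The check is one of direction and then of logic.

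**Direction of the scale.** Each place where the article gives INCAT a direction:

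| Section | What it says about INCAT | Implied direction |
|---|---|---|
| IgG dependency test period | deterioration is an increase of 1 point or more | higher is worse |
| Primary outcome | 0 is healthy, 10 is the worst state; relapse is an increase | higher is worse |
| Secondary outcomes | improvement after rescue is a fall to the baseline value or lower | lower is better |
| Efficacy evaluation secondary outcomes | improvement in restabilization is a decrease of 1 point or more | lower is better |
| IVIg restabilization period, words | improvement to at least the screening level | score ≤ screening, given the rows above |
| IVIg restabilization period, parenthesis | ≥ the screening score | score ≥ screening |

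The last row is the only one that conflicts. The closest parallel is the rule for improvement after rescue, which also asks for a return to a reference value and is written in the ≤ direction. No visible text restates the randomisation criterion with the other sign, and Fig. 1 is not shown.

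**Logic of the two readings.** Let s be the screening score and e the score at the end of restabilization, each from 0 to 10. There are 11 × 11 = 121 possible pairs: 11 with e = s, and (121 − 11) / 2 = 55 on each side.

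| Reading | e < s (better) | e = s | e > s (worse) | Pairs passing |
|---|---|---|---|---|
| e ≥ s, as printed | 0 of 55 pass | 11 of 11 pass | 55 of 55 pass | 66 |
| e ≤ s, as the words read | 55 of 55 pass | 11 of 11 pass | 0 of 55 pass | 66 |

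The two readings agree only on the 11 equal pairs. With a screening score of 3, the printed sign passes scores 3 to 10 and fails 0 to 2; the words pass 0 to 3. These counts show the logic and are not expected patient frequencies.

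**Does the stability condition repair it?** No. It compares two visits within the restabilization period. A score can be stable at a level worse than screening.

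**Is it an extraction fault?** Unlikely. The ≤ sign comes through correctly elsewhere, for instance in the length of the dependency period in the Abstract and in the age groups of Table 4.

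**The case against.** The strongest reply is that the words govern and the words are right. A patient who entered at 3 and now scores 5 has not improved to the screening level on any ordinary reading; a patient who went from 3 to 2 has. The sign looks like shorthand for being at least as good. Anyone who has read the rest of the article would be unlikely to withdraw a patient for getting better. This stands, and it makes the point a contradiction between a sentence and its own gloss, not a deliberately chosen faulty rule.

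A second reply is that this is a condensed article, written after recruitment had closed with 172 patients randomised (Trial status). Its printed sign could have affected enrolment only if the full protocol, which is not shown, carries the same sign. The article also reports central eligibility checks and mandatory investigator training (Appropriateness of measurements). This stands too.

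Three stronger inferences are tempting, and the article supports none of them:

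- A reader might infer that the trial was filled with patients who had not restabilised. No text shows that anyone was admitted or withdrawn on the printed sign.
- A reader might infer that such patients would have too little room to worsen by 1 point, which would blunt the contrast with placebo. A patient at 5 still has 10 − 5 = 5 points of room. A ceiling would matter only near 10, and nothing places patients there.
- A reader might infer that the randomisation system tested this criterion. The section on Randomization and masking says that data critical for randomisation were sent through it, but not that INCAT was compared with the screening value there.

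What the reply does not remove is the contradiction. The sentence and its restatement cannot both be the criterion, and no visible text says which one prevails.

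**Conclusion.** The criterion is wrong as written: it is an internal inconsistency in an operative rule. That conclusion rests only on the article's own definitions of INCAT and needs no outside figure.

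The possible harm is conditional. If the full protocol has the correct direction, or if those applying the rule followed the words, the consequence is one misprinted sign and no effect on the data. If the printed sign was applied, every patient whose score differed from screening was classified the wrong way round on this condition. The article gives no distribution of scores, so the number of patients cannot be estimated. The sample size of 58 per arm does not depend on this point.

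The point still deserves correction, because the rule fixes who was eligible for the randomised comparison, and readers need it to judge or repeat the selection.

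**What to change.** 1. Reconcile the parenthesis with its own sentence and with the INCAT direction used in the rest of the article. The wording of the sentence corresponds to a score ≤ the screening score.
2. Confirm which direction the full protocol states and which direction the central eligibility checks used.
3. Only if the printed sign was applied there, list the affected randomised patients as eligibility deviations and take the list to the blind data review meeting, which already decides on exclusions from particular analyses. The article describes the study as not yet complete, so this could be done before unblinding.

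The cost is one symbol in the text and one look at the full protocol and the eligibility-check specification. If step 3 is triggered, add one listing that compares the screening and baseline INCAT scores, both of which are already collected.

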#### SC treatment period

Three-arm randomization will be performed: one group will receive IgPro20 at 0.2 g/kg bw plus placebo to match the volume in all three groups, one group will receive IgPro20 at 0.4 g/kg bw, and one group will receive only placebo. The total dose/volume of IgPro20 will be calculated on the basis of the bw. The weekly SC infusion of IgPro20 or placebo will be performed on 1 or 2 consecutive days in two sessions using special infusion pumps. Multiple injection sites and two pumps may be used depending on the total volume to be administered. The maximum rate is 20 mL/h in week 1, and 35 mL/h for subsequent infusions. The maximum volume per injection site is 20 mL/site in week 1 and 50 mL/site for the subsequent infusions. Patients are advised to change the injection site(s) with each administration.

Patients (or their caregiver) will be trained to apply SC home therapy during the first four SC treatment sessions at the site. If needed, up to four additional trainings will be offered. Patients will also receive detailed written instructions. To ensure compliance, patients are instructed to follow the treatment instructions carefully and to contact the treating physician/study nurse to discuss any problems with SC infusion.

Patients will bring their used, partially used, and unused vials of IgPro20/placebo every visit to the site. Treatment compliance will be monitored through a drug accountability form checking the unique vial numbers used by a patient and the recorded infusion scheme. A completion visit will be performed at SC week 25 for patients who complete the SC treatment period. Patients experiencing a CIDP relapse during the SC treatment period will receive, within 1 week, IgPro10 as IVIg rescue medication (2 g/kg bw) and will undergo a completion visit before the start of the rescue medication. Patients who withdraw for any other reason will undergo the completion visit within a week of discontinuation.

